### Fear of childbirth

3.2. 

Within the treatment group we expect a significant reduction in FoC symptoms following EMDR therapy, a significantly larger reduction in FoC symptoms, a significantly lower percentage of caesarean sections (elective and unplanned), lower health care costs, and a more positive childbirth experience in the treatment group, as compared to the CAU group.

Not least importantly, in both arms we do not predict EMDR therapy to lead to significantly more obstetric or neonatal complications than CAU.

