## Objectives

3. 

Our main objective is to assess the safety and efficacy of EMDR therapy for pregnant women with PTSD after previous childbirth or FoC. The following hypotheses are tested:

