### Statistical analyses

4.8. 

Descriptive statistics will be used to evaluate demographic, clinical (obstetrical and psychological) baseline characteristics of both arms. All data will be analysed according to intention to treat analysis: the data of all randomized subjects will be analysed using the groups (treatment vs. CAU) as defined at randomization. In both conditions symptoms will be measured at regular intervals, in order to monitor treatment results over time. The treatment group and CAU group will be compared on all outcomes, which will be analysed with linear mixed models (LMM). Baseline scores will be included as covariates, time as a categorical variable, and treatment condition as a fixed effect. The intercept will be treated as a random effect. Furthermore, we will use Chi-squared tests and independent *t*-tests to compare both treatment conditions at different times (alpha level 0.05), or Fisher’s Exact test and Mann–Whitney U-test when appropriate. Effect sizes from change in symptoms between baseline and post-treatment antepartum, and post-treatment postpartum will be calculated with Cohen’s d. Safety is objectified by measuring worsening of FoC/PTSD symptoms, neonatal and obstetrical outcomes, dropout, and determining the presence of adverse events. However, our study is not powered upon these safety measures, therefore this outcome will be shown descriptively.

All analyses will be performed using SPSS version 22.0 (IBM Corp, 2013).

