If EMDR therapy proves to be safe and effective during pregnancy in treating PTSD after childbirth and FoC, these are strong arguments for standard screening pregnant women for these psychological conditions, and to refer them for treatment in an early phase of pregnancy.

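### Safety is part of the main objective and is worded as a tested hypothesis of no significant excess of complications, without a margin; this conflicts with the descriptive safety analysis, and non-significance at 25 or 60 per arm cannot support safety

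*Protocol article*

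**What the plan says.** Four places in the protocol article bear on this.

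- **Section 3 (Objectives):** "Our main objective is to assess the safety and efficacy of EMDR therapy for pregnant women with PTSD after previous childbirth or FoC". The next sentence introduces what follows as hypotheses under test: "The following hypotheses are tested".
- **Section 3.2 (Fear of childbirth, under Objectives):** the safety item in that list reads "in both arms we do not predict EMDR therapy to lead to significantly more obstetric or neonatal complications than CAU". No margin or tolerable excess is attached. The words about both arms appear to mean the PTSD and FoC trials.
- **Section 4.8 (Statistical analyses):** "Safety is objectified by measuring worsening of FoC/PTSD symptoms, neonatal and obstetrical outcomes, dropout, and determining the presence of adverse events". The next sentence adds that "our study is not powered upon these safety measures, therefore this outcome will be shown descriptively". Earlier in the same section, the groups are to be compared on every outcome, with chi-squared or t-tests at 0.05, or Fisher's exact and Mann–Whitney tests where appropriate.
- **Section 5 (Discussion):** "If EMDR therapy proves to be safe and effective during pregnancy in treating PTSD after childbirth and FoC, these are strong arguments for standard screening".

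Section 4.7 derives the sample sizes from CAPS and WDEQ scores alone. The article gives no expected complication rate and no power for safety.

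**The concern.** The sections give safety three different roles. In Section 3 it is a hypothesis tested by significance, in Section 4.8 it is a description, and in the Discussion it is something that could be proved. A prediction of no significant excess is met whenever a test fails to reject, and small samples make that outcome likely whether or not harm exists. Without a margin, the hypothesis also never says how much excess would be acceptable.

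This matters because Section 2.2 notes that clinicians may fear that trauma-focused therapy in pregnancy could harm mother or foetus. Readers will bring that question to the results, and the Discussion links the answer to standard screening and referral. A non-significant p-value reported as the Section 3.2 prediction confirmed would look like an answer without bounding the harm that remains possible.

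**Working it through.** **1. The plan's own figure.** Section 4.7 uses one-sided 0.05, power 80%, d = 0.8 (PTSD) and d = 0.5 (FoC). From n = 2(1.645 + 0.842)²/d², the results are 12.37/0.64 = 19.3, so 20, and 12.37/0.25 = 49.5, so 50. The one-sided t-test gives 21 and 51. The stated 21 and 50 are reproduced. Adding 20% gives 21 × 1.2 = 25.2 and 50 × 1.2 = 60, matching the planned 25 and 60 per arm. Safety plays no part in these sizes.

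**2. Chance of missing a true doubling.** The control risk is not in the documents, so a range is assumed. For each pair of event counts, the two binomial probabilities were multiplied and summed over all pairs in which EMDR has more events and the two-sided p-value is at most 0.05. The chi-squared statistic is uncorrected: z = [(x_E − x_C)/n] / √[2p̄(1 − p̄)/n]. One minus the sum is the chance of missing the doubling, with all randomized women observed:

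| Assumed risk, CAU → EMDR | PTSD, 25 per arm: chi-squared / Fisher | FoC, 60 per arm: chi-squared / Fisher |
|---|---|---|
| 2% → 4% | 99% / >99% | 93% / 99% |
| 5% → 10% | 92% / 99% | 83% / 91% |
| 10% → 20% | 83% / 91% | 67% / 75% |
| 20% → 40% | 65% / 77% | 32% / 40% |
| 30% → 60% | 38% / 49% | 8% / 11% |

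Hand check with the normal approximation, 10% v 20% and n = 60: (0.10 × √60 − 1.96 × √(2 × 0.15 × 0.85)) / √(0.09 + 0.16) = (0.775 − 0.990)/0.5 = −0.43. Power is 33%, so 67% are missed. With n = 25, (0.5 − 0.990)/0.5 = −0.98. Power is 16%, so 84% are missed, close to the exact 83%.

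**3. Sensitivity.**
- *Sidedness.* Section 4.8 does not state it. A one-sided 0.05 chi-squared test in the direction of harm misses a doubling from 5%, 10% and 20% in 83%, 73% and 54% of PTSD trials, and in 71%, 54% and 22% of FoC trials.
- *Attrition.* If the planned 20% also applied to obstetric records (20 and 48 per arm), a doubling from 10% is missed in 86% and 71% (two-sided chi-squared). Records may be more complete than questionnaires, so this is a pessimistic case.

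**4. Size needed.** For 80% power to detect a doubling (two-sided 0.05), 435, 199 and 82 women per arm are needed at control risks of 5%, 10% and 20%.

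**5. What an interval would show if the risks were truly equal.** The half-width of the 95% interval for the risk difference is 1.96 × √(2p(1 − p)/n):

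| Common risk | PTSD, n = 25 | FoC, n = 60 | Excess that is a doubling |
|---|---|---|---|
| 5% | 12.1 points | 7.8 points | 5 points |
| 10% | 16.6 points | 10.7 points | 10 points |
| 20% | 22.2 points | 14.3 points | 20 points |

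Centred on zero, the interval still contains a doubling in both trials at 5% and 10%, but at 20% only in the PTSD trial. On the ratio scale the FoC upper limit at 20% is 2.05, so that case is borderline. The normal approximation is rough at 5% with n = 25.

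**6. Zero events.** No event among 25 treated women leaves a one-sided 95% upper limit of 1 − 0.05^(1/25) = 11.3%. Among 60 it is 1 − 0.05^(1/60) = 4.9%.

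**The case against.** The best defence is that Section 4.8 already concedes the point. It says that safety is not powered and will be described, it names no success criterion, and it defines safety more broadly than complications. Section 3.2 phrases a prediction rather than a decision rule, the Discussion sentence is conditional and joint with efficacy, and the Abstract speaks only of giving more insight. On this reading, the authors never intended a test to settle safety.

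Much of this stands. A reader might infer that the trials will declare EMDR safe on a non-significant p-value; no passage says so. A reader might also infer that confidence intervals will be omitted, or that the lack of a combined safety estimate is an error. A descriptive analysis does not exclude intervals, and a condensed article may leave both to the full protocol or analysis plan. Section 4.2 treats the two studies as separate trials, and their obstetric risk may differ because only the FoC trial can include nulliparous women. Pooling is therefore an option, not an obligation.

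The defence does not remove the conflict. Section 4.8 leaves the Section 3.2 hypothesis and the Discussion wording in place, and its general provision for testing every outcome at 0.05 makes a p-value on complications likely to appear. The disclosure of low power is a reason to withdraw the hypothesis, not to keep it.

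**Conclusion.** The concern holds in a limited form. Sections 3 and 3.2, Section 4.8 and the Discussion must be reconciled, and absence of a significant excess at 25 or 60 per arm should not be offered as evidence of safety. Under a two-sided chi-squared test, the weakness is severe in both trials for complications at about 5% or less (a doubling missed in 83% to 99%). At 10% it is still severe in the PTSD trial (83%) and substantial in the FoC trial (67%).

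It is tempting to go further and say that the trials would almost always find no significant excess even if complications doubled. The documents do not support that. The figures rest on control risks that the article does not give, and in the FoC trial the chance of missing a doubling falls to 32% at 20% → 40% and 8% at 30% → 60%. Section 2.1 cites a trial in which only 47.5% of controls had an uncomplicated vaginal delivery, so a broad composite could be common. The calculations also assume independent events and, outside the sensitivity check, complete obstetric data.

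**What to change.** 1. **Section 3.2:** drop the hypothesis of no significant excess. Replace it with an estimation aim consistent with Section 4.8: to estimate the difference in risk of key obstetric and neonatal complications between EMDR and CAU.
2. **Section 4.8:** for those complications, report risk differences with 95% confidence intervals in each trial, using a method suited to small counts. State that a non-significant difference will not be read as evidence of safety.
3. **Discussion:** reword the sentence on EMDR proving safe, so that any safety conclusion is limited to the excess risk that the upper confidence limit excludes.
4. **Optional:** a supplementary table combining both trials (85 v 85), stratified by trial. At a 10% risk the half-width would be 1.96 × √(2 × 0.1 × 0.9/85) = 9.0 points, against 10.7 in the FoC trial alone.

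If the published text cannot be changed, the same statements can go into the analysis plan before the data are analysed, and into the results paper.

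The cost is wording and a little extra analysis of data already being collected, with no additional participants. The safety conclusion becomes more modest. Keeping a formal claim of no excess would require a stated margin, and these sizes could not meet a tight one: for illustration, a 5-point margin at a 10% risk needs about 566 women per arm (one-sided 0.025, 80% power).

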## Design/methods

4. 

### Participants

4.1. 

Participants eligible for screening for the OptiMUM-study are women with a gestational age of 8–20 weeks, who master the Dutch language (written and spoken). Exclusion criteria are age <18 years old, current psychological treatment, intermediate or high suicide risk (based on the mini international neuropsychiatric interview-plus; MINI-plus), or severe psychotic disorder, such as schizophrenia or current psychosis (based on MINI-plus). Participants are recruited from one university hospital, two teaching hospitals and several community midwifery practices in Amsterdam, the Netherlands..

### Design

4.2. 

Patients will be randomized to either the EMDR therapy group or CAU group on a 1:1 basis by block randomization. The randomization is done by an independent computer program. FoC and PTSD after childbirth have their own randomization program, and therefore can be seen as two separate randomized controlled trials with overlapping design (see Figure 1). The randomization procedure will not balance sites, and no other stratification variables are used since there are no prognostics factors known regarding EMDR response among pregnant women. The study was approved by The Medical Research Ethics Committee of the OLVG Hospital, and is registered as NL4930410014 and NL4930510014. The study is registered prospectively in the Dutch trial register (www.trialregister.nl) as NTR5123 and NTR5122.

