## Abstract

**Background**: Approximately 3% of women develop posttraumatic stress disorder (PTSD) after giving birth, and 7.5% of pregnant women show a pathological fear of childbirth (FoC). FoC or childbirth-related PTSD during (a subsequent) pregnancy can lead to a request for an elective caesarean section as well as adverse obstetrical and neonatal outcomes. For PTSD in general, and several subtypes of specific phobia, eye movement desensitization and reprocessing (EMDR) therapy has been proven effective, but little is known about the effects of applying EMDR during pregnancy.

**Objective**: To describe the protocol of the OptiMUM-study. The main aim of the study is to determine whether EMDR therapy is an effective and safe treatment for pregnant women with childbirth-related PTSD or FoC. In addition, the cost-effectiveness of this approach will be analysed.

**Method**: The single-blind OptiMUM-study consists of two two-armed randomized controlled trials (RCTs) with overlapping design. In several hospitals and community midwifery practices in Amsterdam, the Netherlands, all eligible pregnant women with a gestational age between eight and 20 weeks will be administered the Wijma delivery expectations questionnaire (WDEQ) to asses FoC. Multiparous women will also receive the PTSD checklist for DSM-5 (PCL-5) to screen for possible PTSD. The clinician administered PTSD scale (CAPS-5) will be used for assessing PTSD according to DSM-5 in women scoring above the PCL-5 cut-off value. Fifty women with childbirth-related PTSD and 120 women with FoC will be randomly allocated to either EMDR therapy carried out by a psychologist or care-as-usual. Women currently undergoing psychological treatment or women younger than 18 years will not be included. Primary outcome measures are severity of childbirth-related PTSD or FoC symptoms. Secondary outcomes are percentage of PTSD diagnoses, percentage caesarean sections, subjective childbirth experience, obstetrical and neonatal complications, and health care costs.

**Results**: The results are meant to provide more insight about the safety and possible effectiveness of EMDR therapy during pregnancy for women with PTSD or FoC.

**Conclusion**: This study is the first RCT studying efficacy and safety of EMDR in pregnant women with PTSD after childbirth or Fear of Childbirth.

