
Women who are pregnant for the first time may also experience anxiety symptoms during pregnancy. Overall, about 7.5% of pregnant women experience a pathological fear of childbirth (FoC) (Adams, Eberhard-Gran, & Eskild, 2012; Söderquist, Wijma, Thorbert, & Wijma, 2009). FoC has been found in both nulliparous women who have not experienced childbirth before (primary FoC), as well as in multiparous women (women with a previous birth, whether one or more) in whom a negative or traumatic previous childbirth experience often plays a role (secondary FoC) (Hofberg & Ward, 2003; Størksen, Garthus-Niegel, Vangen, & Eberhard-Gran, 2013). Therefore, it is to be expected that (subclinical) PTSD is accompanied by FoC. FoC appears to be more common in nulliparous women compared to multiparous women (Rouhe, Salmela-Aro, Halmesmäki, & Saisto, 2009). Several studies found that the concept of FoC is multifaceted, including – but not limited to – fear of pain, the baby dying or being handicapped, loneliness, lack of support, or being concerned, or embarrassed about, one’s own appearance while giving birth (Garthus-Niegel, Størksen, Torgersen, Von Soest, & Eberhard-Gran, 2011; Huizink, Mulder, Robies De Medina, Visser, & Buitelaar, 2004). Women with FoC may attempt to avoid pregnancy or even decide to terminate the pregnancy, or request (and receive) a caesarean section (Raïsanen et al., 2014; Størksen, Garthus-Niegel, Adams, Vangen, & Eberhard-Gran, 2015). Moreover, FoC has been found to be associated with increased risk of emergency caesarean section (Ryding, Wijma, Wijma, & Rydhström, 1998), and a sixfold increased risk of PTSD following childbirth (Söderquist et al., 2009).

Prevalence rates of women avoiding pregnancy because of posttraumatic stress symptoms after previous childbirth or FoC are unknown. Avoidance symptoms can include avoiding conversations with healthcare providers about childbirth-related mental health problems, such that even women with the most severe symptoms might not be noticed. Awareness among healthcare providers and women themselves, and an available effective treatment may help to improve quality of life for them and their partners.

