### Posttraumatic stress disorder

3.1. 

Within the treatment group we expect a significant reduction of the severity of PTSD symptoms and percentage of PTSD diagnoses present following EMDR therapy. We expect a significantly larger reduction in PTSD symptom severity and a significantly lower percentage of PTSD diagnoses in the treatment group after completion of the EMDR sessions, compared to the CAU group. Furthermore, we predict a significantly lower percentage of caesarean sections (both elective and unplanned), a significantly more positive childbirth experience, and significantly lower health care costs in the treatment group.

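### Caesarean section is assigned to a linear mixed model that cannot apply to it, with only an unadjusted test as alternative; the cost is precision, not validity

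*Protocol article*

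**What the plan says.** Section 4.8 (Statistical analyses) sets one rule: "The treatment group and CAU group will be compared on all outcomes, which will be analysed with linear mixed models (LMM"). It lists the terms: "Baseline scores will be included as covariates, time as a categorical variable, and treatment condition as a fixed effect", with a random intercept. It then adds simpler tests: "Furthermore, we will use Chi-squared tests and independent" *t*-tests, with Fisher's exact and Mann–Whitney tests as substitutes. No regression model for a binary outcome is named.

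The Abstract names caesarean section among the secondary outcomes: "Secondary outcomes are percentage of PTSD diagnoses, percentage caesarean sections, subjective childbirth experience, obstetrical and neonatal complications, and health care costs". Section 3.1 states a directional hypothesis for the PTSD trial: "we predict a significantly lower percentage of caesarean sections (both elective and unplanned"). Section 3.2 predicts the same for the FoC trial.

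Section 4.2 (Design) does not balance sites and adds that "no other stratification variables are used since there are no prognostics factors known regarding EMDR response among pregnant women". Section 4.4 (Procedure) shows that parity is known at screening, since it decides who completes the PCL-5. The FoC trial takes women of any parity. The PTSD trial needs an earlier birth as index trauma, so all its women are multiparous. Section 4.8 says obstetric baseline characteristics will be described, but previous caesarean is nowhere named as a variable. The same section reports obstetric and neonatal safety outcomes descriptively, because the study is not powered for them.

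**The concern.** The rule for all outcomes does not fit this one. A woman has one delivery in the trial, so time has no levels, there is no baseline score to enter, and a random intercept cannot be separated from residual error. The reader is left with a chi-squared or Fisher test, and the article does not say which method governs.

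The reason for not stratifying concerns response to EMDR. Mode of delivery is a different outcome, and a woman's obstetric history may predict it whatever her response to therapy. An analysis that ignores a strong predictor gives a wider interval than it need and leaves any chance imbalance in place. Caesarean section carries a significance hypothesis in both trials, and the Discussion expects prevented caesareans to help offset treatment costs, so a less noisy estimate is worth having.

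**Working it through.** **The plan's own figures.** Sample size is stated only for the symptom scores: one-sided 0.05, power 80%. With n = 2(1.645 + 0.842)²/d² = 12.37/d²:
- d = 0.8 gives 19.3, so 20 per group (exact *t*-test 20.03, so 21; stated 21).
- d = 0.5 gives 49.5, so 50 per group (exact *t*-test 50.15; stated 50).
- Attrition: 21 × 1.2 = 25.2 and 50 × 1.2 = 60, against 25 and 60 stated.

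These reproduce. No figure is given for caesarean section, so everything below rests on assumed rates.

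**Power for caesarean section (two-sided 0.05, unadjusted).**

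| Assumed rates | 60 per arm | 25 per arm |
|---|---|---|
| 30% vs 20% | 24% | 12.5% |
| 40% vs 25% | 42% | 20% |
| 40% vs 20% | 67% | 33.5% |

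**Chance imbalance without stratification.** The SD of the between-arm difference in a binary factor is √(2p(1−p)/n).
- p = 0.5, n = 60: √(0.5/60) = 9 points. By simulation, a gap of 10 points or more occurs in about 32% of trials, and 15 or more in 12%.
- p = 0.3, n = 25: √(0.42/25) = 13 points.

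In the PTSD trial, suppose 30% have had a caesarean and that this raises the risk by 30 to 60 points. A one-SD imbalance then shifts the caesarean difference by 0.13 × 30 to 0.13 × 60, or 3.9 to 7.8 points. If 30% of women overall deliver by caesarean, the standard error of the unadjusted difference is also √(2 × 0.3 × 0.7/25) = 13 points. The shift is already part of that error: (3.9/13)² = 9% to (7.8/13)² = 36% of the variance.

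**Gain from adjustment, FoC trial.** Assume 50% nulliparous (caesarean risk 30%), 35% multiparous without previous caesarean (10%) and 15% multiparous with previous caesarean (70%).
- Overall risk: 0.15 + 0.035 + 0.105 = 0.29; variance 0.29 × 0.71 = 0.2059.
- Variance between the three groups: 0.5(0.01)² + 0.35(0.19)² + 0.15(0.41)² = 0.0379, or 18% of the total. Simulation under no effect gives 19%.
- Parity alone: multiparous risk is (0.035 + 0.105)/0.5 = 28%, against 30% in nulliparous women. Variance between the two groups is 0.0001, or about 0.05% of the total.

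Simulation, 60 per arm, 6,000 trials per scenario:

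| | Unadjusted chi-squared | Adjusted logistic |
|---|---|---|
| Type I error, no effect | 5.6% | 5.0% |
| Power, conditional OR 0.4 | 40% | 44% |
| Mean risk difference, OR 0.4 | −0.129 | −0.128 |
| SD of risk difference, OR 0.4 | 0.0750 | 0.0686 |

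The variance ratio at OR 0.4 is 0.837, about 16% lower. A plain linear model on the 0/1 outcome, which is what remains of the mixed model with one observation per woman, gives 5.3% type I error and 40% power. It offers nothing over the unadjusted test.

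**The case against.** The mixed-model description plainly has repeated symptom scores in mind, and chi-squared or Fisher is the natural reading for a proportion. The rule for all outcomes may be loose drafting in a condensed article, and a covariate list for a secondary outcome commonly sits in an analysis plan that is not shown. Much of this stands. The missing list is not the fault; the fault is a stated rule that does not fit a named outcome. The unadjusted test is also valid, and choosing adjustment is a matter of precision on an unpowered secondary outcome. That stands in full.

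A reader might infer more, which the article does not support:
- *That imbalance makes the caesarean result biased.* The standard error already carries it, and the mean estimate does not change with adjustment.
- *That the lack of stratification is an error.* Simple block randomisation is sound, and the reason given is only narrower than the outcomes it has to serve.
- *That previous caesarean is already recorded.* This is plausible from the obstetric baseline data and patient records, but not stated.
- *That complications need adjusted models too.* Section 4.8 reports the safety outcomes descriptively.
- *That parity belongs in the FoC primary model.* The remark that "FoC appears to be more common in nulliparous women compared to multiparous women" concerns prevalence. It does not speak to change in WDEQ score, and the model already holds the baseline score.

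**Conclusion.** The point holds as a matter of model fit and efficiency. As written, the mixed model cannot be applied to caesarean section, and the alternative named leaves precision unused. The gain is modest: in the assumed FoC scenario, about 16% less variance and four points of power at no cost in patients. It depends on the assumed shares and risks, above all on a strong effect of previous caesarean; the article gives no caesarean rates by parity or history. Under those assumptions parity by itself would add almost nothing, so the factor must separate multiparous women by previous caesarean. Validity of the test and the primary symptom conclusions are not in question.

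**What to change.** Before unblinding, amend section 4.8 or the analysis plan as follows.

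1. Limit the linear mixed model to repeatedly measured scores.
2. FoC trial: analyse caesarean section by logistic regression on treatment and one pre-specified obstetric-history factor with three levels (nulliparous; multiparous without previous caesarean; multiparous with previous caesarean). Report a standardised risk difference with 95% CI: each woman's predicted risk under both arms, averaged and subtracted.
3. PTSD trial: adjust at most for previous caesarean, with a small-sample method such as Firth's. Keep Fisher's exact test if events are too few, with the threshold set in advance.
4. Confirm that previous caesarean is captured in the obstetric baseline data, and if not, extract it from the obstetric records.

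The cost is wording, one or two extra parameters (felt most in the 50-woman trial), and a check that the single software package named in section 4.8 can produce these estimates. Sample size and randomisation stay as they are.
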